## Abstract

**Background:** Metabolic bariatric surgery is a highly effective and long-lasting treatment for obesity and related chronic conditions. Women of reproductive age represent the largest group undergoing these procedures. Observational studies suggest an increased risk of preterm birth and impaired foetal growth in this population, though the underlying mechanisms remain unclear. A key hypothesis is that altered glucose metabolism, characterised by frequent hypoglycaemia and glycaemic fluctuations, may contribute to these adverse outcomes. While glycaemic variability following metabolic bariatric surgery has been documented, its pattern during pregnancy and impact on pregnancy outcomes are still underexplored. **Methods:** In this Belgian multicentre prospective cohort study, we will investigate glycaemic patterns during pregnancy in women who have undergone metabolic bariatric surgery. Women aged 18–45 years with a confirmed singleton pregnancy up to 11 weeks and 6 days and a history of Roux-en-Y gastric bypass or sleeve gastrectomy will be eligible for inclusion. Women with pregestational diabetes or those taking medication known to interfere with glucose metabolism will be excluded. All participants will receive blinded continuous glucose monitoring (Dexcom^®^ G6) for a 10-day period at four time points throughout the pregnancy. Foetal body composition and growth will be measured during routine ultrasound; skinfolds will be measured in the neonate. The primary outcome is the association between mean glycemia and glycaemic variability on continuous glucose monitoring and birth weight. The planned sample size is ninety-five women. Linear mixed models for repeated measurements will be used for analysis. Confounders such as smoking, micronutrient deficiency, and surgery-to-conception interval will be added to the model as covariates. In a second exploratory phase, each participant in the surgical group will be matched with a control participant—without a history of metabolic bariatric surgery—based on pre-pregnancy BMI and age. Control participants will undergo the same study procedures, allowing for exploratory comparison of glycaemic patterns and other study outcomes. **Discussion:** This prospective longitudinal study will be the largest study using continuous glucose monitoring to investigate glucose metabolism during pregnancy after metabolic bariatric surgery and its impact on foetal growth and newborn body composition. **Trial registration**: ClinicalTrials.gov: NCT05084339. Registration date: 15 October 2021.

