#### 2.8.9. CGM

The Dexcom G6^®^ CGM system with blinded receiver (Dexcom, San Diego, CA, USA) is a CE-labelled device that is approved for use in pregnancy [37] and provides real-time continuous measurement of interstitial glucose levels via a small sensor, which is inserted in the subcutaneous skin of the abdomen or upper arm. The device is disposable and without the need for calibrations. One sensor session can record glucose values for up to 10 days. This sensor has a high accuracy, as reflected by the mean absolute relative difference (MARD) of 8.7% for wear on the posterior upper arm in pregnancy [37]. CGM will be performed at four distinct timepoints, each involving a single sensor session. Continuous CGM throughout the entire pregnancy was not pursued due to the substantial cost implications for this investigator-initiated academic trial. Additionally, continuous monitoring would likely increase participant burden, potentially affecting recruitment, adherence, and retention. The study design was therefore optimised to align with routine clinical care. Of note, previous research in uncomplicated pregnancies has demonstrated that CGM-derived metrics remain relatively stable across all three trimesters. The Dexcom G6^®^ sensor will be used in a blinded manner, so that glucose values are masked from the participant to encourage normal daily behaviour and obtain unbiased insights into maternal glucose patterns. This approach avoids potential issues associated with unblinded CGM, which may inadvertently cause anxiety, disrupt sleep, and lead to unnecessary carbohydrate intake in response to device-alerted hypoglycaemia. Such behaviours could influence participant responses and provoke post-bariatric hypoglycaemia, thereby biassing glucose data. Furthermore, the clinical significance of hypoglycaemia detected by CGM during pregnancy after MBS is not well established.

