#### 2.9.1. Sample Size and Power Calculation

The sample size (n = 95) was calculated based on the best available data on CGM in pregnancy with MBS [40,41]. The study provides 80% power to detect a moderate association (effect size = 0.3) between glycaemia measures (mean and variability) and birth weight at a significance level of *p* < 0.05. Repeated CGM measurements (four one-week periods per participant) were accounted for using a cluster size of four and assuming an interclass correlation (ICC) of 0.5. A drop-out rate of 30% was assumed, in the sense that 30% of all measurements would be missing. The sample size was decided considering adjustment for four variables in the analysis. A Bonferroni correction will be applied to control for multiple comparisons, resulting in a 2.5% test-wise significance level.

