#### 2.9.2. Statistical Methods

##### Primary and Secondary Analyses (MBS Group)

The primary analysis will be performed using linear mixed models, adjusted for confounders. Mean glycemia refers to the mean interstitial glucose level measured via CGM throughout pregnancy. Glycaemic variability reflects fluctuations in blood glucose levels and is quantified using variables such as SD, CV, and MAGE derived from CGM. Repeated measurements will be used for the primary outcome analysis, with mean glycemia and glycaemic variability treated as continuous outcome variables, and birth weight as the explanatory variable. To account for clustering due to repeated measures, linear mixed models will be used with a random intercept for the subject. Confounders such as smoking, hypertension, nutrient deficiencies, insufficient gestational weight gain, and time from surgery will be added to the model as covariates to determine the independent association between birth weight and glycaemic parameters. Variables will be considered confounders if they are associated with both birth weight and glycaemic parameters. Linear slopes with 95% confidence intervals will describe the association between glycaemic parameters and birth weight. No specific action is taken to deal with missing CGM results given the fact that the analysis model is likelihood-based and known to provide unbiased results under the fairly general assumption of missingness at random [42]. Statistical analysis will be performed by SAS version 9.4; all tests will be two-sided with significance set at *p* < 0.05.

Secondary outcomes, including time spent <54 mg/dL and hyperglycaemic thresholds (>120 mg/dL and >140 mg/dL), will be analysed analogously.

Third, associations between glycaemic patterns and binary neonatal outcomes, including SGA and birth defects, will be assessed similarly using linear models for repeated measurements. Mean differences with 95% confidence intervals will be estimated between cases with and without the specified adverse outcome.

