##### Exploratory Comparative Analyses

The control group will be manually matched in a 1:1 ratio based on age and pre-pregnancy BMI before participation. A comparison of both groups on participant characteristics such as parity, insufficient GWG, hypertension, micronutrient deficiencies, and smoking status will be performed using Fisher exact tests. The comparison between the MBS and control group on birth weight and glycaemic measures will be performed using linear mixed models with a random intercept to account for clustering by matching. Confounders will be included as covariates in the model in case they were shown to differ between groups. Group comparisons on binary variables such as adverse pregnancy outcomes will be performed using a similar approach, applying generalised linear mixed models for binary responses.

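### The surgical-versus-control comparison names one random intercept, for the matched pair; applied to session-level CGM data, it would understate the standard error of the group difference

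*Protocol article*

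**What the plan says.** The Exploratory Comparative Analyses part of section 2.9.2 covers two kinds of outcome, birth weight and the CGM measures, in one sentence. It says that the group comparison for both "will be performed using linear mixed models with a random intercept to account for clustering by matching". That is the only random effect named there.

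The two outcomes have different data structures. Birth weight is recorded once per woman. For glycaemia, section 2.8.9 states: "CGM will be performed at four distinct timepoints, each involving a single sensor session". The controls have the same sessions, according to the Abstract: "Control participants will undergo the same study procedures, allowing for exploratory comparison of glycaemic patterns and other study outcomes". Section 2.9.5 has the CGM metrics loaded into the database by woman and by visit.

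For the surgical group alone, section 2.9.2 gives a different structure and its reason: "To account for clustering due to repeated measures, linear mixed models will be used with a random intercept for the subject". That sentence stands under the heading for the MBS-group analyses. It is not repeated or referred to in the comparative paragraph.

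**The concern.** Each pair contains one surgical woman and one control, so the group difference is a within-pair contrast. Its error comes mainly from differences between women in the same pair. A pair intercept removes what the two women share. It does not represent what is particular to each woman. Without a woman-level term, that variation falls into the residual and is averaged over sessions as if each session gave new information about the group difference.

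At stake are the standard errors, intervals and p-values for the glycaemic comparisons between surgical and control women, which are the first exploratory objective in section 2.3. The Discussion also expects the data to feed later meta-analyses, where standard errors that are too small would give the study too much weight. An exploratory label excuses low power and multiple testing. It does not excuse an invalid standard error.

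**Working it through.** **Inputs from the protocol.** Four sessions per woman (2.8.9); sample size derived "using a cluster size of four and assuming an interclass correlation (ICC) of 0.5"; 30% of measurements missing (2.9.1); 1:1 matching, so 95 pairs if every surgical participant is matched; two-sided tests at 5% (2.9.2).

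**Assumptions.** The protocol does not say how much of the ICC the pair explains; 0 to 50% is taken. ICCs of 0.3 and 0.7 are taken as alternatives to 0.5.

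**The plan's own figure.** The protocol gives no error rate for this comparison. Its sample size does show how the ICC is meant. For a correlation of 0.3, two-sided 2.5% and 80% power:
- n0 = ((2.241 + 0.842) / atanh(0.3))² + 3 = 102.2
- plus four covariates: 106.2
- times (1 + 3 × 0.5)/4 = 0.625: 66.4
- divided by 0.7: 94.8, so 95

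The stated 95 is reproduced with 0.5 as the correlation between sessions of the same woman.

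**Model.** Let the total variance be 1, split into pair (vp), woman within pair (vw) and session (ve), with vp + vw = ICC. With m sessions per woman, per pair:
- residual mean square under a pair-only intercept = (m·vw + (2m − 1)·ve)/(2m − 1)
- variance that the model assigns to the difference = 2 × residual mean square / m
- true variance of the difference = 2 × (vw + ve/m)
- SE ratio = √(true / assigned)
- rejection rate at nominal 5% = 2 × (1 − Φ(1.96 / SE ratio))

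The number of pairs cancels in the ratio.

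**Worked case: ICC 0.5, m = 4, vp = 0.** Residual mean square = (4 × 0.5 + 7 × 0.5)/7 = 0.786. Assigned variance = 2 × 0.786/4 = 0.393. True variance = 2 × (0.5 + 0.125) = 1.25. SE ratio = √(1.25/0.393) = 1.78. Rejection rate = 27%.

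**ICC 0.5, four complete sessions:**

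| vp | vw | Assigned variance | True variance | SE ratio | Rejection, formula | Rejection, simulated |
|---|---|---|---|---|---|---|
| 0 | 0.50 | 0.393 | 1.25 | 1.78 | 27% | 26% |
| 0.10 | 0.40 | 0.364 | 1.05 | 1.70 | 25% | 25% |
| 0.20 | 0.30 | 0.336 | 0.85 | 1.59 | 22% | 21% |
| 0.25 | 0.25 | 0.321 | 0.75 | 1.53 | 20% | not run |

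The simulations fitted the pair-only model by REML to 95 pairs, with 3,000 data sets per setting.

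**With 30% of measurements missing**, m averages 0.7 × 4 = 2.8. For vp = 0, the assigned variance is 2 × [(2.8 × 0.5 + 4.6 × 0.5)/4.6]/2.8 = 0.574 and the true variance is 2 × (0.5 + 0.5/2.8) = 1.357. The SE ratio is 1.54 and the rejection rate 20%. For vp = 0.20 it is 16%. Simulation with sessions missing at random gave 18-21%.

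**Other ICCs, complete data**, with the pair explaining 0 to 40% of the ICC: 14-18% at ICC 0.3 and 31-35% at ICC 0.7.

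**Correct alternative.** A paired test on one mean per woman is equivalent, with complete data, to adding a woman-within-pair intercept. In the same simulations it rejected 4.5-5.7% of the time, including with 30% missing.

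**The case against.** A reader might infer that the protocol definitely treats the four sessions as independent and that false-positive rates of 20-30% will follow. The text does not go that far, for four reasons.

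- The comparative paragraph does not say that the pair intercept is the only random effect, nor that the subject intercept is dropped. It could be naming the further source of clustering that matching adds to the repeated measures dealt with just before.
- It does not say that sessions enter as separate rows. The same section states: "Mean glycemia refers to the mean interstitial glucose level measured via CGM throughout pregnancy". That wording allows one value per woman, for which a pair-only intercept is correct. Birth weight stands in the same sentence and is one value per woman.
- The upper figures need four complete sessions, and the protocol itself plans for 30% of measurements to be missing.
- This is a condensed article, and details of an exploratory model are often left to a fuller document.

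The first three limit the claim, and the result is stated conditionally for that reason. They do not remove it. The subject intercept is introduced only for the surgical-group analyses, and the definition of mean glycaemia stands next to a statement that repeated measurements are used. Section 2.3.1 has the measures taken at four time points per woman, and no averaging is mentioned for the comparison. Session-level rows are therefore a natural reading, and a programmer who follows the paragraph literally would fit the pair intercept alone. The fourth does not apply: the paragraph is not silent on the random structure. It fixes one, and that structure suits only one of the two data types it covers.

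**Conclusion.** The point holds conditionally. If glycaemic measures are analysed by session with the random effect as written, the standard error of the group difference is understated 1.53- to 1.78-fold at ICC 0.5 with complete data, and a nominal 5% test rejects about 20-27% of the time. With the planned missing measurements the rate is about 16-21%. Over assumed ICCs of 0.3 to 0.7 with complete data it is about 14-35%. These figures rest on a planning ICC that was set for the surgical cohort and on an assumed pair share. In every setting examined, the rate is roughly three to seven times nominal.

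If one summary per woman is analysed, the stated model is valid. The birth-weight comparison is unaffected either way. So is the primary analysis, which uses surgical women only and has its own subject intercept. Because the comparison is labelled exploratory throughout, the severity is moderate and does not put the trial's main conclusion at risk.

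**What to change.** In the comparative paragraph of section 2.9.2, separate the two kinds of outcome and state the unit of analysis:

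- For glycaemic measures analysed by session, fit random intercepts for the matched pair and for the woman within the pair.
- Alternatively, state that each woman contributes one summary value per glycaemic measure, analysed with the pair intercept.
- For birth weight, keep the pair-only intercept.

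This costs one sentence and, for the session-level option, one further random-effect statement in the program. Design, visits and data collection do not change. Compared with the pair-only model on session rows, intervals for the glycaemic comparisons become wider, and they are then correct. A categorical visit effect, or the same nesting for a repeated binary measure, may be added but is not needed to correct this error.

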#### 2.9.3. Trial Management

This is an academic research trial. University Hospitals Leuven (UZ Leuven) is the sponsor and has responsibility for the overall management of the study.

#### 2.9.4. Data Management

Every site will be opened after a first initiation visit. During the study conduct, the coordinating investigator will conduct periodic quality assurance visits of all study-sites to ensure that the protocol is being followed. A first visit for all sites will be performed within three months after the first inclusion and thereafter at least once yearly. The coordinating investigator of the study may review source documents to confirm that the data recorded on CRF pages is correct. It is important that the investigator(s) and their relevant personnel are available during the quality assurance visits and audits or inspections, and that sufficient time is devoted to the process.

The collection, processing, and disclosure of personal data, such as patient health and medical information, is subject to compliance with applicable personal data protection and the processing of personal data (Regulation (EU) 2016/679 of the European parliament and of the council of 27 April 2016 on the protection of natural persons with regard to the processing of personal data and on the free movement of such data, and repealing Directive 95/46/EC (GDPR, General Data Protection Regulation)).

Each participant will receive a subject identification number to ensure confidentiality of the data. Only the local study team will have access to the file with the identifying data. The subject number will be put on the page of each visit. All data collected in this study will be referred to by subject identification number only. During the study, all data will be stored locally in each hospital at the department of obstetrics or endocrinology in a secure manner following the Belgian legislation. Participants will be asked specifically to give an informed consent for the use of their data for future studies, and for storage of biological materials. At any given time, they can ask for data and materials to be destroyed.

All amendments will be reported to the ethics committees that previously provided a favourable opinion on the study protocol.

#### 2.9.5. Datatypes Collection and Preservation of Data

All obtained data will be collected in REDCap (Research Electronic Data Capture) version 14.5.35 (Vanderbilt University, Nashville, TN, USA). Data collected in this study will be referred to by subject identification numbers only. Data will first be recorded by trained staff at each site on standardised source worksheets and thereafter in REDCap. Glucose monitoring data will initially be collected via the manufacturer’s cloud-based software using subject identification numbers. At the coordinating site, these data will be periodically exported. CGM metrics, described in Section 2.3.1, Section 2.3.2 and Section 2.3.3, will be obtained using Excel formulas and GlyCulator, a free, open-access online platform [43]. The resulting dataset will then be uploaded—per subject and per study visit—to the corresponding data instrument in REDCap using Excel-based import files. Blood samples will be stored for a max. of 10 years at the biobank of UZ Leuven to allow for additional analyses such as new biomarkers. Data will be stored during the study in each study site. Long-term storage of data lasting at least 25 years will be undertaken in collaboration with a designated data storage provider.

## 3. Discussion

This large longitudinal cohort study aims to investigate whether pregnancy following MBS is associated with altered maternal glucose profiles, as assessed by CGM, and whether these alterations are linked to differences in foetal growth and newborn body composition. Outside of pregnancy, altered glucose patterns after MBS have been well-documented [18]. Emerging data suggests that pregnancies following RYGB are marked by significant glycaemic variability, including frequent episodes of both hyper- and hypoglycaemia. However, most studies to date are small and cross-sectional. Bonis et al. first reported wide glucose fluctuations and substantial hyperglycaemia in mid-pregnancy CGM profiles of post-RYGB women, resembling patterns seen in the non-pregnant post-RYGB population [40]. Leutner et al. similarly found increased glycaemic variability, including more frequent day and nighttime hypoglycaemic events compared to pregnant controls [41]. In a larger retrospective study, Gohier et al. found that 73% of women had abnormal time in range (TIR), and found associations between hypoglycaemia and prematurity, while SGA was paradoxically linked to lower hypoglycaemia exposure [44]. Additionally, an observational cross-sectional study comparing pregnancies after RYGB and SG found that while mean glucose levels were similar, women post-RYGB experienced greater glycaemic variability and spent less time in the target glucose range, indicating more pronounced glucose fluctuations following RYGB [45]. The only longitudinal data come from Stentebjerg et al., who performed CGM across all trimesters, demonstrating that, compared to BMI- and parity-matched controls, these pregnant women spent more time in both hyperglycaemia and hypoglycaemia. They also observed a modest association between increased time spent in hypoglycaemia and SGA outcomes [21]. Overall, while evidence points to a distinct glycaemic profile in post-RYGB pregnancies, none of these earlier studies were sufficiently powered to show the implications on foetal growth [21].

This GLORIA study aims to include pregnant women with a history of both SG and RYGB, as these procedures are currently the most performed worldwide. This approach will enable us to include a representative population of pregnant women post-MBS. A second phase of the study consists of matching each participant in the cohort on a one-to-one basis with a control participant, based on age and pre-pregnancy BMI. This will allow for further, exploratory comparisons. The study will provide comprehensive data on key pregnancy outcomes, including gestational weight gain, micronutrient status, and foetal and neonatal biometry throughout pregnancy. These data, along with glycaemic patterns, will help future meta-analyses by enabling comparisons across studies using the same methods.

This study protocol has several inherent limitations. First, although the study involves multiple centres across Belgium, it only includes centres in the Flemish-speaking part. The generalizability of findings to other ethnic populations or healthcare systems may be limited. Additionally, several analyses—such as those involving metabolomics data and patient-reported outcomes—are exploratory in nature. As such, they will not provide definitive evidence but rather identify trends or associations that can inform the design of future confirmatory studies.

Nevertheless, this study is important and innovative because it will be the largest investigating glycaemic variability throughout pregnancy after MBS, measuring at four distinct time points. Our hypothesis is that it is not the woman’s weight, nor her caloric intake, but rather her (glucose) metabolism that is a key factor influencing the observed pregnancy outcomes. In other words, to improve outcomes for these pregnancies, the focus should not necessarily be on achieving appropriate gestational weight gain, but rather on preventing glycaemic variability through education and the use of novel technologies.

